## 402 **S2. Definition of outcomes**

403

### 404 *Primary Outcome*

405 The primary outcome of VFD will be calculated as the sum of all episodes of invasive respiratory support, which require an endotracheal tube in situ,  
406 from start of CPB and censored at 28 days after CPB start. Patients who die within this time period will be assigned a value of zero for the VFD outcome.  
407 Ventilated days do not include non-invasive ventilation or high-flow nasal cannulae. Patients who receive a tracheostomy will be counted as ventilated  
408 as long as they receive positive pressure ventilation through the tracheostomy. The individual components of VFDs (duration of invasive respiratory  
409 support from start of CPB within the first 28 days, and death within the first 28 days) will also be presented.

410

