## 3 STUDY OUTCOMES

### 3.1 Primary outcome

**Length of mechanical ventilation** as defined as the duration of respiratory support for all episodes with an endotracheal tube in situ for the first 28 days post randomisation. The outcome will be reported using ventilator free days (VFD). A systematically zero value will be assigned for patients who die to allow important weight to death as the most pejorative outcome.

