### **Definitions**

- **Length of mechanical ventilation** is defined as the duration of invasive respiratory support for all episodes with an endotracheal tube in situ for the first 28 days post randomisation. The outcome will be reported using ventilator free days (VFD). A systematically zero value will be assigned for patients who die to allow important weight to death as the most pejorative outcome.
  - For infants with tracheostomies, ventilation support will be considered completed at the time point when the patient reaches pre-intervention baseline respiratory support levels
- **LCOS** is defined as the inability of the myocardium to provide adequate oxygen delivery (DO2) to the tissue. DO2 measurements are not feasible in daily practice, hence accepted surrogate measures are commonly used. For the purpose of this study, **LCOS** will be defined as[6]:

- blood lactate level greater than 4 mmol/l with an oxygen extraction of greater than 35% (SaO2-SvO2 gradient >35%); within the first 48 hours postoperatively and/or
- high inotrope requirement: Inotrope requirement will be calculated by means of the Vasoactive-Inotrope Score (VIS) (2): VIS = dopamine dose (mcg/kg/min) + dobutamine dose (mcg/kg/min) + 100 x adrenaline dose (mcg/kg/min) + 100 x noradrenaline dose (mcg/kg/min) + 10 x milrinone dose (mcg/kg/min) + 10,000 x vasopressin dose (U/kg/hr). A score ≥15 indicating low cardiac *output syndrome*.
- Initiation of **ECLS** in theatre or postoperatively in intensive care with presence of LCOS
- **Death** within 28 days of the operation
- Length of stay in intensive care
- Hospital length of stay
- Renal failure
- Inhaled NO
- Sedation and delirium scores post surgery
- Functional performance at PICU discharge, at hospital discharge, and during follow-up (in comparison to baseline functional status, if available)
- 1-year follow-up surveys (QoL, Ages and Stages Questionnaire, socioeconomic status)
- 1-year follow-up neurodevelopmental assessment with neuropsychologist (at sites where the funding and infrastructure allows): using Bayley-III, including cognitive, language, motor, social-emotional and adaptive behaviours

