## **Sample size**

Pilot study data demonstrated a 66 hour (0.33 SD) reduction in VFDs associated with the study intervention [26]. Assuming a minimally clinically significant small effect size (0.2 SD), 90% power, two-sided alpha level of significance of 5%, 10% withdrawals, and 15% increase in sample size to account for a non-normal distribution of VFD, 1,320 patients are required (660 per group).

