## **Outcome measures**

The definition and detail of calculation of outcome measures can be found in the Supplementary Appendix (Section S2), alongside the Stata scripts written to calculate these outcomes (available on GitHub (16)). Briefly, the outcomes are:

- Primary outcome measure: VFDs within 28 days from start of CPB
- Secondary outcome measures:

- Individual VFD components (i.e. duration of mechanical ventilation, death within 28 days after CPB start)
- Individual and components of composite measure of LCOS, and/or ECLS within 48 hours after CPB start and/or death within 28 days after CPB start;
- Length of PICU stay after CPB start;
- Length of hospital stay after CPB start;
- Process of care measures:
  - Treatment with ECLS within 48 hours after CPB start;
  - Duration of postoperative time spent with open chest including unplanned chest reopening after CPB start;
  - Treatment and duration of treatment using inhalational nitric oxide postoperatively after CPB start;
  - Treatment and duration of treatment of postoperative renal replacement therapy (includes peritoneal and continuous venous-venous haemodialysis) after CPB start;
- Physiological descriptors:
  - Postoperative troponin levels during the first 24 hours postoperatively;
  - Severity and duration of postoperative organ dysfunction; and
  - Postoperative acute kidney injury (AKI) and serum creatinine levels measured during the first 24 hours.

For the purposes of analysis and reporting, LCOS within 48 hours after CPB start, ECLS within 48 hours after CPB start, death within 28 days after CPB start and length of stay in PICU and hospital are classified as potentially patient-important secondary outcomes. The remaining secondary outcomes will be reported to describe patient physiology and processes of care only.

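### The SAP's calculation rule for ventilator-free days describes ventilated time, so with death set to zero the primary-outcome scale is incoherent as written

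*Combined protocol and SAP*

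**What the plan says.** The SAP's Outcome measures section names ventilator-free days (VFD) as primary and refers to Supplementary Appendix S2, and to posted Stata code, for the calculation. S2 says: "The primary outcome of VFD will be calculated as the sum of all episodes of invasive respiratory support". The window runs "from start of CPB and censored at 28 days after CPB start". It continues: "Patients who die within this time period will be assigned a value of zero for the VFD outcome". The same paragraph lists the duration of invasive support and death as components of VFD.

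Protocol sections 3.1 and 7.2 (Definitions) define length of mechanical ventilation over all intubated episodes "for the first 28 days post randomisation", to be reported as VFD. They explain the zero: "A systematically zero value will be assigned for patients who die to allow important weight to death as the most pejorative outcome".

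The SAP's primary hypothesis is that NO raises VFD, and protocol 11.2 is powered to show an increase. Yet the SAP's sample-size section reports that the pilot showed "a 66 hour (0.33 SD) reduction in VFDs", and protocol 11.2 also describes the pilot benefit as a reduction.

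For infants with tracheostomies, protocol 7.2 says "ventilation support will be considered completed at the time point when the patient reaches pre-intervention baseline respiratory support levels". S2 instead counts a patient who receives a tracheostomy as ventilated for as long as positive pressure is delivered through it.

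**The concern.** A sum of ventilation episodes is the complement of VFD. The zero assigned to death is sensible only on the VFD scale, where zero is the worst value. On the scale that S2 describes, zero means no ventilation at all. One sentence of S2 therefore assumes one scale and the next assumes the other.

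The primary test is Mann-Whitney, so the result depends entirely on how children are ranked. Someone reproducing the analysis from the SAP text would compute the wrong variable. If the code subtracts from 28, it departs from the written rule; if it follows the written rule, the analysis is wrong. Either way, the prespecified definition does not settle the primary outcome, and two interim comparisons of that outcome (at 660 and 1,000 patients) had already been made when the SAP was written.

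**Working it through.** **1. The plan's own sample size.** Inputs from the SAP's Sample size section: effect 0.2 SD, power 90%, two-sided alpha 5%, 10% withdrawals, 15% for non-normality, 660 per group.

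n per group = 2(1.960 + 1.282)² / 0.2² = 525.4, rounded up to 526.

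- 526 × 1.15 × 1.10 = 665.4 per group, about 1,331 in total
- 526 × 1.15 / 0.90 = 672.1 per group, about 1,344 in total
- 526 × 1.25 = 657.5 per group, 1,315 in total

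All three are within 2% of 1,320. The calculation uses a standardised effect, so the wording of S2 does not affect it.

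**2. Scoring the same children two ways.**

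| Child | S2 as written | 28 minus ventilated days, death = 0 |
|---|---|---|
| Dies by day 28 | 0 | 0 |
| Alive, 1 day ventilated | 1 | 27 |
| Alive, 2 days | 2 | 26 |
| Alive, 10 days | 10 | 18 |
| Alive, 27 days | 27 | 1 |
| Alive, 28 days | 28 | 0 |

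The middle column can be read in two directions:

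- *Lower is better* (the natural reading of ventilated time): death ranks ahead of every survivor with any ventilation. This contradicts the reason the protocol gives for the zero.
- *Higher is better* (the direction in the SAP hypothesis): death stays at the bottom, but a survivor ventilated for all 28 days ranks best and the most quickly extubated survivor ranks just above death.

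Neither gives the intended order. In the right-hand column death has the lowest score, shared only with survivors ventilated throughout.

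**3. How much the placing of deaths could matter.** Reversing a whole scale leaves a two-sided Mann-Whitney p-value unchanged; only the placing of deaths relative to survivors changes the test. An illustrative simulation rests on assumptions that are not in the documents: 594 analysed per arm (660 × 0.9), lognormal ventilation time with mean 80 hours and log-SD 1.2, identical in both arms, 1,000 runs per scenario. Entries are the percentage of runs significant for NO / for control.

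| Mortality, control v NO | S2 as written, lower better | 28 minus ventilated days |
|---|---|---|
| 3% v 3% | 2.2 / 3.5 | 2.1 / 3.1 |
| 2% v 5% | 12.8 / 0.1 | 0.1 / 15.3 |
| 5% v 10% | 32.2 / 0.1 | 0 / 33.5 |

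Under that reading a mortality imbalance pushes the test the wrong way. With equal mortality there is little difference.

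**4. The 66-hour figure.** 66 / 0.33 implies an SD of 200 hours. Protocol Table 1 (pilot children under 2 years) gives mean ventilation of 97.8 hours for control and 65.1 hours for NO, a difference of 32.7 hours, about half of 66. The two need not agree, because VFD also penalises deaths. But the documents do not show how 66 hours was obtained, so changing the word reduction to increase would not by itself make the statement right.

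**5. Time origin and tracheostomy.** The protocol starts the 28 days at randomisation and the SAP at CPB start. The SAP's Randomisation section says the gap between them varies with site logistics; its length is not given. The two tracheostomy rules would part for a child already receiving positive pressure through a tracheostomy before surgery: one stops counting at the return to baseline, the other continues.

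**The case against.** The strongest reply is that no informed reader would code S2 literally. The outcome's name, the direction of the hypothesis, the protocol's rationale for the zero, the list of components within S2, and the separate rows for VFD and ventilation duration in SAP Table 3 all point to 28 minus ventilated days. A calculation must already have existed for the interim analyses, and the code is said to be posted. This stands as evidence of intent. It does not supply the missing formula, and it does not show that the code matches.

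A reader might infer that the SAP makes death the best possible score, or that the primary comparison is reversed. The documents do not support that. Death is best only if lower is taken as better, and the SAP's stated direction is the opposite. No analysis run in the wrong direction is shown.

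A reader might also count 26 to 66 misplaced deaths (2% to 5% of 1,320). That range borrows the general perioperative death rate in protocol 2.1; it is not 28-day mortality in this under-2 population, which also excludes several high-risk groups.

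On the lesser points, the SAP uses CPB start consistently. The tracheostomy rules may address different children (those who have one and those who receive one), and chronic ventilator dependency is an exclusion, so that conflict is arguable and probably affects few.

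**Conclusion.** The written calculation rule for the primary outcome is wrong and should be corrected. S2 describes ventilated time, assigns zero to death, and cannot be ranked sensibly in either direction. For a survivor the written and intended scores differ by |28 − 2d|, where d is days ventilated: 24 points at 2 days and 26 at 27 days.

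This is very probably a drafting error. The conclusion concerns the text, not any analysis performed, and the posted code could not be examined. Ranking death ahead of all survivors requires both that lower is read as better and that every survivor has some ventilation after CPB start, which is a reasonable assumption in this setting. The simulation shows direction only. Sample size and alpha are not affected.

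The difference in time origin is real but of unknown size. The tracheostomy rules need reconciling, and the 66-hour statement needs its source checked as well as its direction.

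**What to change.** - In S2, replace the calculation sentence with: VFD equals 28 minus the total days (hours/24) of invasive ventilation, over all episodes, from CPB start to day 28; VFD is 0 for any death by day 28; higher values are better.
- Before unblinding, confirm that the posted code, including that used for the two interim analyses, computes this quantity. Record the check, and declare the change as the SAP requires for changes after publication.
- Use one time origin in the protocol and the SAP.
- Reconcile the tracheostomy scoring in protocol 7.2 with S2, and state which children each part covers.
- In protocol 11.2 and the SAP's Sample size section, trace the 66 hours to its source, state the quantity and pilot subset it describes, and correct its direction.

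The cost is a few sentences of amended text and a code review. No new data, patients or change in sample size are needed, unless the code proves to follow the written rule. In that case the interim comparisons should be rerun with the corrected score.

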### 411 *Secondary Outcomes*

412 The main secondary outcome is defined by a composite of presence of LCOS, extracorporeal life support (ECLS), or all-cause death.

- 413 • The presence of LCOS (21) will be calculated as a binary variable by evaluating the relevant data items at the following time-points: admission  
414 to PICU, and after six hours, 12 hours, 24 hours, and 48 hours post-PICU admission, or until the patient is discharged from PICU (whichever  
415 occurs first). Criteria for LCOS include a blood lactate level (arterial where available, if not then venous) >4 mmol/L and the presence of an  
416 oxygen extraction of greater than 35% ( $\text{SaO}_2\text{-ScvO}_2$  gradient >35%), or a high inotrope requirement operationalised as Vasoactive-Inotrope  
417 Score (VIS)  $\geq 15$  (22, 23). If these criteria are met for at least one of the above listed timepoints, the presence of LCOS is confirmed. If individual  
418 data items required for the calculation of LCOS are missing, then the patient will be assumed not to have had LCOS.

- ECLS post-CPB during the first 48 hours after CPB start.
- Mortality is defined as all-cause death within the first 28 days after CPB start.

Additional secondary outcomes include PICU and hospital length of stay, which will be measured from start time of CPB. In patients discharged alive from the PICU to the ward and readmitted within 72 hours the subsequent PICU admission duration will be added to the index admission. Length of stay (both PICU and hospital) will be censored at 28 days or when the patient was last alive, whichever occurs earlier. Patients who die during their PICU or hospital admission will be assigned the time to event.

Process of care measures will include the use of ECLS (as defined above); duration of time with open chest post-operatively within the first 28 days (as all surgeries will have an open chest during theatre, the time measure will start with admission to PICU, and will include time spent with open chest in cases of emergency secondary reopening); treatment and duration of treatment with inhalational NO from admission to PICU post-operatively within the first 28 days; and treatment and duration of treatment with renal replacement from admission to PICU post-operatively within the first 28 days (defined as the use of peritoneal dialysis or continuous renal replacement therapy [CRRT]). Duration of treatment with inhalational NO post-operatively and duration of treatment with renal replacement post-operatively will be restricted to those patients receiving these treatments.

433 Organ dysfunction will be assessed at admission to PICU, after 24 hours and after 48 hours, and will be defined by using the cardiovascular, respiratory,  
434 renal, neurological, and haematological components of the Paediatric Logistic Organ Dysfunction-2 (PELOD-2) scores (24). If score items are missing  
435 then it will be assumed that value was normal for the purpose of the score.

436

437 Postoperative Acute Kidney Injury was assessed using serum creatinine levels to classify according to Kidney Disease: Improving Global Outcomes  
438 (KDIGO) criteria (25). Because no baseline creatinine values were available, we applied the age-specific thresholds used in PELOD-2 to define the  
439 presumed baseline creatinine values. KDIGO Stage 1 was defined as an increase in creatinine to 1.5 to 1.9 times the presumed baseline; Stage 2 as an  
440 increase 2.0 to 2.9 times; and KDIGO 3 as an increase  $\geq 3.0$  baseline and/or the use of RRT.

441

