### 7.3 Blood Sample Collection for Inflammation analysis

**Biomarker Analysis and Biobanking:** Blood markers for myocardial injury and inflammatory response will be collected on induction of anaesthetics (baseline – pre bypass), at admission to PICU (0 hours – post bypass) and at 12, and 24 hours for the following purposes: i) to test the impact of the intervention on markers of inflammation; ii) to stratify patients in to high- versus low inflammatory groups; iii) to biochemically define responders to the intervention (to identify patient subgroups that are more likely to respond to a specific treatment), iv) to develop improved markers of outcome post cardiac surgery. Collection of blood for biomarker analysis and biobanking is optional and parents will be asked to provide their permission during the consenting process.

**Blood sampling and processing.** *Preoperative baseline* (before onset of cardiac surgery, done by anaesthetist during the induction of the patient once the arterial line has been inserted): 1-2ml of EDTA blood (for DNA), 2.5ml of blood (PAXgene tube for gene expression markers), 1-2ml of serum *Postoperative at 0,12,24 hrs* (in PICU until discharge to the ward): 2.5ml of blood (PAXgene tube - time point 0 only), 1-2ml of serum. The total amount of blood taken is 10-15ml for the entire study duration, which is much less than the amount of blood taken for routine perioperative care tests. The samples will be processed within 30 minutes, centrifuged, aliquotted and immediately frozen. The samples will be kept in a security protected freezer in the each institution, and will be transferred in batch every 12 months to the Centre for Children's Health Research, Brisbane, Australia. Urinary electrolytes and NH4 will be measured from patient urine collected through the

standard IDC at baseline, admission to PICU, and 6-24hours to assess for renal concentration and secretory function. Paired arterial and venous gases will be collected postoperatively at 0,6,12,24,48 hrs (in PICU until discharge to the ward or removal of arterial line, whichever occurs first) to assess for lactate and SaO2-SvO2 gradient. Each arterial or venous blood gas sample requires 0.2mls of blood and would total 2mls across all samples. Routine paired gases are often part of standard clinical care.

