### *Secondary outcome measures*

For binary outcome measures (e.g. LCOS), logistic regression analyses will be used including age group and physiology as fixed effects, and site as a random effect, with unadjusted and adjusted odds ratios (ORs) and 95% CIs reported (Table 3). Survival outcomes (length of PICU stay, length of hospital stay) will be visually presented using a Kaplan-Meier plot and a Cox proportional hazard model will be used to assess differences between treatment groups with

treatment group and stratification variables as fixed effects and site as a random effect (i.e. utilising a shared frailty model). The hazard ratio and 95% CI will be presented as an estimate of treatment effect. Continuous outcomes (e.g. PELOD-2, duration of renal replacement therapy) will be analysed using linear regression adjusting for age group and physiology as fixed effects, and site as a random effect, with mean difference and 95% CI reported. If the residuals demonstrate non-normality, quantile regression will instead be used in the same manner as for the primary outcome. Key assumptions of the models will be tested and reported on (for logistic regression: specification, goodness-of-fit, absence of multicollinearity and absence of influential observations; for survival analysis: proportionality assumption, goodness-of-fit; for linear regression: specification, distribution of residuals, homoscedasticity, absence of multicollinearity, linearity).

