#### *Treatment of missing data*

Missing data will be imputed for the primary outcome measure for any patients are missing one or more components required to calculate VFDs. Fully conditional specification will be used for imputation; the imputation model will include randomised treatment arm, study site and the two study strata variables. Ten sets of imputed data will be created using the methods described for the primary outcome. A pooled common effect estimate and 95% confidence interval will be generated from the imputed datasets.

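### SAP S2 turns unknown LCOS status into no LCOS and missing PELOD-2 items into normal values, and no planned analysis tests either rule

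*Combined protocol and SAP*

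**What the plan says.** SAP S2 (Secondary Outcomes) evaluates LCOS at PICU admission and 6, 12, 24 and 48 hours later, stopping at PICU discharge. A time point is positive if lactate exceeds 4 mmol/L together with an SaO2-ScvO2 gradient above 35%, or if the Vasoactive-Inotrope Score (VIS) is at least 15. Venous lactate may replace arterial lactate. Two consecutive sentences then settle the child's status:

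- "If these criteria are met for at least one of the above listed timepoints, the presence of LCOS is confirmed".
- If individual "data items required for the calculation of LCOS are missing, then the patient will be assumed not to have had LCOS".

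PELOD-2 is assessed at PICU admission, 24 and 48 hours. Where an item is missing, "then it will be assumed that value was normal for the purpose of the score".

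Protocol 7.3 schedules the paired arterial and venous gases at 0, 6, 12, 24 and 48 hours, but only "in PICU until discharge to the ward or removal of arterial line, whichever occurs first".

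LCOS is one of the secondary outcomes that the SAP (Outcome measures) classes as potentially important to patients. It has its own row in SAP Table 3 and enters the composite: "The main secondary outcome is defined by a composite of presence of LCOS, extracorporeal life support (ECLS), or all-cause death". On the analysis: "For binary outcome measures (e.g. LCOS), logistic regression analyses will be used", with odds ratios reported.

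On missing data the SAP says: "Missing data will be imputed for the primary outcome measure for any patients are missing one or more components required to calculate VFDs". No other outcome is named there. The sensitivity analysis (SAP, Subgroup and sensitivity analyses) adds CPB duration, surgical complexity, blood prime and sex to the models. It leaves the handling of missing data unchanged.

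**The concern.** The rules treat absence of data as absence of disease. LCOS is the pathway through which the protocol (section 2.2) expects nitric oxide to work, so misclassifying it matters for interpreting the trial as well as for one table row.

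Gaps are to be expected. S2 asks for LCOS data until PICU discharge, while paired gases may stop earlier, when the arterial line comes out. A child still in PICU after that point has scheduled time points without a gradient, and the venous fallback in S2 covers lactate only.

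Children who die in theatre or before an assessment also have no values. For VFD the plan handles death explicitly, by assigning zero. LCOS taken alone and PELOD-2 have no equivalent provision.

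**Working it through.** **1. The two LCOS sentences applied to four children**

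| Child | One-positive sentence | Missing-items sentence | Actual status |
|---|---|---|---|
| A: VIS at least 15 on admission, gradient missing at 12 h | LCOS | could be read as no LCOS | LCOS |
| B: lactate above 4, gradient missing after line removal, VIS below 15 throughout | not confirmed | no LCOS | unknown |
| C: dies before any PICU assessment | not confirmed | no LCOS | unknown |
| D: VIS below 15 and lactate 4 or less throughout, gradient missing | not confirmed | no LCOS | no LCOS |

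Child A shows the conflict. Children B and C are coded negative on either reading although their status is unknown. Child D is coded correctly, because the lactate alone rules out the lactate-plus-gradient criterion.

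**2. What the rest of the plan recovers**

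Death within 28 days and ECLS within 48 hours of CPB start are events in the composite, and death sets VFD to zero. So C is recovered in the composite and in VFD, but not in the LCOS row. A surviving child B without ECLS is not recovered in either LCOS or the composite.

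**3. Equal loss in both arms**

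The documents give no missingness rate for LCOS or PELOD-2, so there is no planned figure to reproduce. Inputs: pilot LCOS rates in children under 2 years, 35.8% control and 12.3% nitric oxide (protocol Table 1), taken as true; an assumed share m of LCOS cases recoded as no LCOS in each arm.

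Observed rate = true rate × (1 − m). Odds ratio = [p_NO/(1 − p_NO)] / [p_C/(1 − p_C)].

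| m | Control | NO | Difference (points) | Odds ratio |
|---|---|---|---|---|
| 0 | 35.8% | 12.3% | 23.5 | 0.25 |
| 10% | 32.2% | 11.1% | 21.2 | 0.26 |
| 20% | 28.6% | 9.8% | 18.8 | 0.27 |
| 30% | 25.1% | 8.6% | 16.5 | 0.28 |

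The risk ratio stays at 12.3/35.8 = 0.34 throughout.

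For a smaller assumed effect, 30% against 24% with 660 per arm, power falls from 69% with no loss to 63% at m = 10% and 56% at m = 20%.

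**4. Unequal loss, no true effect**

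Assume 35.8% in both arms.

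- 5% of cases lost in control and 15% in NO: 0.358 × 0.95 = 34.0% against 0.358 × 0.85 = 30.4%. This is a false difference of 3.6 points, odds ratio 0.85. With 660 per arm the standard error is √[(0.3401 × 0.6599 + 0.3043 × 0.6957)/660] = 0.0257, so z = 0.0358/0.0257 = 1.39. The chance of a significant result favouring NO is P(Z > 1.96 − 1.39), about 28%.
- 10% lost in control and 5% in NO: 32.2% against 34.0%. This is a false difference of 1.8 points against NO, odds ratio 1.08, with about a 10% chance of significance in that direction.

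**5. Deaths and PELOD-2**

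Protocol 2.1 gives a perioperative mortality of 2% to 5%. Applied to 1,320 children this is 26 to 66 deaths. Only deaths before the 24 or 48 hour assessment bear on PELOD-2, and the documents do not give that number.

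**The case against.** A reader might infer that any missing item makes a child LCOS-negative, even with a VIS of 15 or more already recorded. If all 15 item-by-time cells (five time points; lactate, gradient, VIS) had to be complete, independent missingness of 1%, 2% or 5% per cell would force 1 − 0.99^15 = 14%, 1 − 0.98^15 = 26% or 1 − 0.95^15 = 54% of children to negative. The documents do not support taking this as the plan. The rule does not say any item, the preceding sentence confirms LCOS on one positive time point, and a VIS of 15 suffices without a venous sample. The SAP also points to Stata scripts for the outcome calculations, which may settle the order. What remains is that the SAP text does not settle it.

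Other points on that side are fair:

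- Many lines come out because the child is well, so no LCOS is often the right guess. VIS needs no arterial line, venous lactate is allowed, and time points after PICU discharge are not required. This reduces the number of indeterminate children but does not remove them.
- Outcome items are verified against source for every enrolled patient (SAP, Data monitoring). That can recover recorded values, but not samples never taken.
- On the planned odds-ratio scale, equal loss changes little. This stands.
- Secondary results are declared exploratory, and PELOD-2 is there only to describe physiology. Table 3 summarises it by medians, which a few early deaths would hardly move. This limits the importance of the point.
- Giving dead children the worst PELOD-2 rank would turn an organ-dysfunction score into a mortality composite. That is a different estimand, and it is not proposed here.

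**Conclusion.** The point holds in a limited form. A stated rule codes unknown LCOS status as absence, the SAP text leaves open whether an observed positive prevails, and neither the LCOS nor the PELOD-2 rule is tested. The composite is protected for deaths and early ECLS, but not for misclassified survivors without ECLS. The primary outcome is unaffected.

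The size cannot be determined. The illustrations rest on assumed loss rates and on pilot LCOS rates taken as true. Under equal loss the risk difference shrinks in proportion and the odds ratio barely moves. Under unequal loss a spurious difference can arise.

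Two stronger inferences should be resisted. The first is that the bias must fall mainly on control children. That presumes that nitric oxide works and that sicker children have more gaps, and the documents establish neither. The second is that 26 to 66 dead children would be scored normal on PELOD-2. That range is at most an upper bound: it applies a general surgical mortality rate to a trial that excludes several high-risk groups, and it counts deaths after 48 hours. The SAP also does not say that a dead child receives a score. It only fails to exclude it.

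**What to change.** Amend SAP S2 and the missing-data section before unblinding:

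1. Any observed positive time point gives LCOS = yes, whatever else is missing.
2. LCOS = no only when the observed data up to PICU discharge rule it out. At each time point this means VIS below 15 and either lactate 4 mmol/L or less or a gradient of 35% or less. Most well children with missing gradients can be classified this way without imputation.
3. Treat the remaining children as missing. Multiply impute LCOS with the planned fully conditional specification model, adding observed VIS, lactate, ECLS and death, and derive the composite from the imputed LCOS. Children with death or ECLS are already composite events.
4. Keep the current rule, missing equals no LCOS, as a sensitivity analysis.
5. Report LCOS and PELOD-2 missingness by arm and time point.
6. For PELOD-2, apply the normal-value default only to unmeasured items in children alive at that time point. Do not score children already dead as normal. Report deaths before 24 and 48 hours by arm beside the scores.

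The cost is SAP wording and modest extra programming. No new data are needed and the primary analysis does not change. For a child who dies before any PICU assessment, imputed LCOS is a convention, so the composite should be read first for those children.
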